### 3.8 Study calendar

| Events \ Timing                                                        | Day of Delivery - Screening (Day 0) | Day after discharge (Day 1-2) | Between Day 1-Day 30 (Additional Visits-Optional) | Day 14 | Day 21 | Day 30 | Day 84 | Day 180 |
|-------------------------------------------------------------------------------|-------------------------------------|-------------------------------|---------------------------------------------------|--------|--------|--------|--------|---------|
| Informed consent                                                              | X S                                 |                               |                                                   |        |        |        |        |         |
| Eligibility Confirmation                                                      | X S                                 |                               |                                                   |        |        |        |        |         |
| Ask for contact information                                                   | X S                                 |                               |                                                   |        |        |        |        |         |
| Randomization                                                                 | X S                                 |                               |                                                   |        |        |        |        |         |
| Collection of information about delivery, obstetrical and medical history and | X S                                 |                               |                                                   |        |        |        |        |         |

|                                                                                                                                     |   |   |   |     |     |     |     |     |
|-------------------------------------------------------------------------------------------------------------------------------------|---|---|---|-----|-----|-----|-----|-----|
| information on the baby from hospital chart                                                                                         |   |   |   |     |     |     |     |     |
| Hospital discharge within 24 hours for vaginal birth and 48 hours for C-section                                                     | X |   |   |     |     |     |     |     |
| Maternal care and neonatal care (jaundice screening using transcutaneous bilirubinometer and weight gain assessment) at the clinic. |   | X |   |     |     |     |     |     |
| Breastfeeding support at clinic                                                                                                     |   | X | X |     |     |     |     |     |
| Additional medical care at clinic                                                                                                   |   |   | X |     |     |     |     |     |
| Collection of medical data from visits at clinic                                                                                    |   | X | X |     |     |     |     |     |
| Demographics survey                                                                                                                 |   |   |   |     |     | X S |     |     |
| Edinburgh Postnatal Depression Scale                                                                                                |   |   |   |     | X S | X S |     |     |
| Breastfeeding local complications survey                                                                                            |   |   |   | X S |     | X S |     |     |
| Breastfeeding survey                                                                                                                |   |   |   | X S |     | X S | X S |     |
| Use of resources survey                                                                                                             |   |   |   | X S |     | X S | X S |     |
| Self-efficacy survey                                                                                                                |   |   |   | X S |     | X S | X S |     |
| Mother Satisfaction Survey                                                                                                          |   |   |   |     |     |     | X S |     |
| 6 month follow up survey                                                                                                            |   |   |   |     |     |     |     | X S |

Index: X = Women assigned to the breastfeeding clinic program will be completing these events

S = Women assigned to the standard care will be completing these events

## 4 Statistics

### 4.1 Sample size

Based on an estimated 50% rate of exclusive breastfeeding at 3 months in the control group, 200 patients per group will be needed to detect a 15% relative difference in the intervention group ( $\alpha=0.05$ ,  $\beta=0.9$ , one-sided test). Assuming an attrition rate of 15% (i.e. loss to follow up, unsuitability, or other unanticipated events), we set a target of **230 participants per group** making a total of **460** women. Accounting for the logistical concern of making full use of the nursing staff, lactation consultants, and family physicians at the clinic, we decided to apply a 1:2 ratio for control to intervention allocations and determined that 154 and 306 patients are needed for the control and intervention groups respectively (maintaining significance level, power, and effect size).

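### Section 4.1's 200 per group does not follow from a 15% relative increase on 50%; it best matches a 15-percentage-point difference, and the effect as written has about 41% to 44% power, not 90%

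*Protocol*

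**What the plan says.** Section 4.1 of the protocol holds the whole sample-size argument for the primary outcome.

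- Control rate: "Based on an estimated 50% rate of exclusive breastfeeding at 3 months in the control group".
- Effect and size: "200 patients per group will be needed to detect a 15% relative difference in the intervention group".
- Error rates: alpha 0.05, a value of 0.9 labelled beta, and a "one-sided test".
- Loss: "Assuming an attrition rate of 15"%, which leads to "230 participants per group making a total of 460 women".
- Final allocation: for clinic staffing reasons the ratio becomes 1:2, and the authors "determined that 154 and 306 patients are needed for the control and intervention groups respectively", described as "maintaining significance level, power, and effect size".

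No section gives the expected rate in the intervention arm, and none says that the 15% is an absolute difference.

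**The concern.** On a 50% base, a 15% relative change and a 15-point absolute change differ by a factor of two: 7.5 points against 15 points. Required sample size varies roughly with the inverse square of the difference, so the choice moves it about fourfold. A figure of 200 per group looks far too small for the smaller effect and about right for the larger one.

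This is the design effect for the primary outcome. If section 4.1 stands, the protocol claims 90% power for an effect that the trial would miss more often than detect. Anyone who relied on that claim when interpreting a non-significant result would overrate what the trial can rule out.

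**Working it through.** **Inputs, all from section 4.1.** Control rate p1 = 0.50; one-sided alpha 0.05 (z = 1.6449); power 0.90 (z = 1.2816); attrition 15%; final allocation 154 control and 306 intervention. The printed beta of 0.9 is read as power. Taken literally it would mean 10% power, for which about 12 per group would do.

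**Sample-size formula** (two proportions, pooled variance under the null, d = p2 − p1, p̄ the mean rate):

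n per group = [1.6449·√(2p̄(1−p̄)) + 1.2816·√(p1(1−p1) + p2(1−p2))]² / d²

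Continuity correction: n_cc = (n/4)·[1 + √(1 + 4/(n·d))]²

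**Step 1: which effect gives the plan's 200?** Try 0.50 versus 0.65, so d = 0.15 and p̄ = 0.575.

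- n = (1.1499 + 0.8856)² / 0.0225 = 184.1, so 185 per group.
- n_cc = 197.3, so 198 per group.
- Unpooled and arcsine formulas give 182 and 185.

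The continuity-corrected figure is within about 1% of 200; the plain one is about 8% below it.

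**Step 2: the effect as written.** 0.50 × 1.15 = 0.575, so d = 0.075 and p̄ = 0.5375.

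- n = (1.1598 + 0.9011)² / 0.005625 = 755.1 per group.
- n_cc = 781.5, so 782 per group.
- Unpooled and arcsine formulas give 753 and 756.
- Relaxing power to 80% still needs 543 to 572, depending on formula.

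No variant comes near 200; the ratio is 755/200 ≈ 3.8. Reading the change as a decrease makes no difference, because the variance is symmetric about 50%.

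**Step 3: power.** With s0 the pooled and s1 the unpooled standard error of the difference, power = Φ[(d − 1.6449·s0)/s1]. The continuity-corrected version subtracts ½(1/n1 + 1/n2) from d. After 15% loss, 154 × 0.85 = 130.9 and 306 × 0.85 = 260.1, so 131 and 260.

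| Intervention rate | Evaluable (control/intervention) | s0 | s1 | Power | Power, corrected |
|---|---|---|---|---|---|
| 57.5% | 200/200 | 0.0499 | 0.0497 | 44.4% | 40.5% |
| 57.5% | 131/260 | 0.0533 | 0.0534 | 40.6% | 36.5% |
| 65% | 200/200 | 0.0494 | 0.0489 | 92.0% | 90.4% |
| 65% | 131/260 | 0.0525 | 0.0528 | 88.6% | 86.4% |

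Worked example, second row: (0.075 − 1.6449 × 0.0533)/0.0534 = −0.238, and Φ(−0.238) = 0.406.

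With no attrition at all, 154/306 gives 45.3% for 57.5% (uncorrected).

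**Step 4: size needed if 15% relative was meant.** At 1:2 the requirement is 566 + 1,132 = 1,698 evaluable (586 + 1,172 = 1,758 corrected). Dividing by 0.85 gives about 2,000 to 2,070 enrolled. Section 4.2 expects 600 over the recruitment period.

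**The case against.** The arithmetic has no good rebuttal: the inputs are complete, no standard formula gives 200 for 57.5%, and no other section reconciles them. The fair objections concern how far the conclusion reaches.

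- **Which term is wrong.** A reader might infer that the authors certainly meant 15 percentage points. The match with 198 makes that likely, but the protocol does not name its formula, and the plain formula gives 185. The documents support an inconsistency and a best match, not proof of intent. A reader might equally infer that the trial is grossly undersized; that holds only if 15% relative was the real target.
- **Which power belongs to which design.** The 41% belongs to 131/260 after attrition; 200/200 gives 44%. The same care applies to the larger effect: 90% holds for 200/200 evaluable, whereas the planned allocation after attrition gives about 89% (86% corrected). Replacing one word while leaving 0.90 against 154/306 would therefore not be accurate either.
- **Judging success by a 95% interval.** A reader might infer from the 95% confidence intervals in section 4.3 that power is lower still. Section 4.1 specifies a one-sided test and section 4.3 mentions intervals for reporting estimates, so the documents do not set that decision rule and it plays no part here.
- **Misreading of a null result.** The protocol states no rule for interpreting a non-significant result, so this is a risk and not something that the plan commits to.
- **The beta label.** Its intended meaning is plain. It is a minor slip that the same edit removes.

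**Conclusion.** Section 4.1 is wrong as written. At a 50% control rate, one-sided alpha 0.05 and 90% power, a 15% relative increase needs about 755 evaluable women per group (782 corrected), against the 200 stated. For that effect the trial has about 44% power at 200/200 and about 41% at the planned allocation after attrition, each about 4 points lower with continuity correction. The stated 200 best fits 50% versus 65%, for which the planned design is close to its target at about 89% (86% corrected).

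This rests on the protocol's own control rate, error rates and attrition, on reading 0.9 as power, and on the normal approximation for two independent proportions without covariate adjustment. The choice of formula shifts the results by a few points and does not change the conclusion.

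**What to change.** The sponsor should check its original calculation and restate section 4.1 with the expected rate in both arms. If enrolment is to stay as planned, the text could read:

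> To detect an absolute difference of 15 percentage points (50% vs 65%, a 30% relative increase) with one-sided alpha 0.05, 200 evaluable women per group give power of about 0.90 (beta 0.10). The planned 154/306 allocation, about 131/260 after 15% attrition, gives about 0.89 (0.86 with continuity correction). Power for a 15% relative increase (50% vs 57.5%) is only about 41%, so a non-significant result does not exclude an effect of that size.

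This costs protocol wording only. The detectable effect becomes less favourable than the one now printed, and enrolment does not change.

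If the original calculation shows that 15% relative was the intended target, wording will not repair it. The 1:2 design would need about 2,000 to 2,070 women enrolled, far beyond the 600 in section 4.2, and the sponsor would have to enlarge the trial or state openly that it is not powered for that effect.

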### 4.3 Statistical analysis

All outcomes will be analyzed based on the intention-to-treat principle, in accordance with the randomization allocations described previously. The primary goal of this study is to test the hypothesis that rates of exclusive breastfeeding at 3 months (defined as the feeding of only the infant's mother's milk for at least 2 weeks prior to collected outcome) will be higher in the group of women attending the post-partum clinic, as compared to those under standard of care. For comparison between intervention and control arms we will employ a generalized estimating equation multivariable regression model to account for prognostic risk factors that have not been sufficiently balanced by randomization. Group and individual level covariates will be included in the model, with recruitment site as the clustering unit to allow for inference at the individual level. This design will also investigate the effect of demographic

drivers such as maternal age, education, parity, etc., on the primary outcome, producing both crude and adjusted risk estimates and their 95% confidence intervals.

Secondary outcomes will be collected by studying the medical data (such as rates of hyperbilirubinemia and self-efficacy) that will be entered in the database by the research staff. This data will be compared across case and control groups using the Pearson Chi-squared, Student's t, or Fisher's exact test, depending on their observed frequencies. We will also compare the statistics and outcomes from the present study with baseline estimates from phase 1. The answers women provide through their questionnaires and surveys will be the main instruments for determining exclusive breastfeeding rates and their behavioral and emotional measurements. For the cost-effectiveness analysis, direct and indirect costs for the intervention and control groups will be compared regarding use of resources (e.g., clinic visits, physician visits, Emergency Department visits, hospital readmission, and indirect cost).

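### Section 4.1 says power is maintained when the same 460 women are re-split 1:2; it falls by about 3 points, and its actual level depends on an effect size stated ambiguously

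*Protocol*

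**What the plan says.** Section 4.1 of the protocol builds the sample size in three steps.

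- **Base size.** "Based on an estimated 50% rate of exclusive breastfeeding at 3 months in the control group", it says that "200 patients per group will be needed to detect a 15% relative difference in the intervention group". The test is a "one-sided test" at α = 0.05, and 0.9 is given as the value of β.
- **Attrition.** "Assuming an attrition rate of 15% (i.e. loss to follow up, unsuitability, or other unanticipated events"), the target becomes "230 participants per group", 460 in all.
- **Allocation.** So that the clinic staff are fully used, a 1:2 control-to-intervention ratio is adopted, and the sponsor "determined that 154 and 306 patients are needed for the control and intervention groups respectively (maintaining significance level, power, and effect size").

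Section 3.2.2 confirms the 2:1 randomisation in favour of the intervention. Section 4.3 describes a regression model for the primary outcome, "producing both crude and adjusted risk estimates and their 95% confidence intervals". It does not say whether the intervals are two-sided or whether they decide the conclusion.

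**The concern.** 154 + 306 = 460 and 230 + 230 = 460. The allocation changed and the total did not. With significance level, effect and total all held fixed, moving away from equal allocation must cost power, so the statement that all three properties are kept cannot be right. The figure also rests on a total that was inflated by multiplying by 1.15 instead of dividing by 0.85.

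What is at stake is the power that a funder, an ethics board or a later reader will attribute to the trial. The size of the shortfall cannot be stated without settling the effect: 200 per group does not follow from a 15% relative difference on a 50% control rate, so a corrected power figure for the 1:2 design needs the effect named first.

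**Working it through.** **Inputs (section 4.1).** Control rate 50%; one-sided α = 0.05 (z = 1.645); target power 90% (z = 1.282), reading the printed β of 0.9 as power; attrition 15%; enrolled 154/306. Intervention rate: 57.5% if the 15% is relative (0.50 × 1.15), 65% if it means percentage points.

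**1. Reproducing 200 per group.** For k intervention women per control, with p̄ = (p₁ + k·p₂)/(1 + k):

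n₁ = [1.645·√(p̄(1−p̄)(1+1/k)) + 1.282·√(p₁(1−p₁) + p₂(1−p₂)/k)]² / (p₂−p₁)²

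At k = 1:

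| Effect | Uncorrected | Continuity-corrected |
|---|---|---|
| 50% vs 57.5% | 756 per group | 782 per group |
| 50% vs 65% | 185 per group | 198 per group |

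Only the 15-point reading comes near 200, and the corrected formula comes closest.

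**2. Attrition.** 200 × 1.15 = 230, but 230 × 0.85 = 195.5, which is below 200. The inflation that leaves 200 is 200/0.85 = 235.3, rounded up to 236 per group (472 in all). At 1:1 the difference is worth about half a point of power: 92.0% at 200/200 against 91.5% at 195.5/195.5 (uncorrected, 50% vs 65%).

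**3. Allocation.** The equal-allocation equivalent of 154/306 is 4 × 154 × 306/460 = 409.8, so 460 women at 1:2 act like about 410 at 1:1. This is the factor 4 × (1/3) × (2/3) = 8/9.

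**4. Evaluable women.** 154 × 0.85 = 130.9 and 306 × 0.85 = 260.1, so about 131/260.

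**5. Delivered power, one-sided 5%.** Power = Φ{(δ − 1.645·s₀)/s₁}, where s₀ is the pooled and s₁ the unpooled standard error. The continuity correction subtracts ½(1/n₁ + 1/n₂) from δ.

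For 131/260 and 50% vs 65%: pooled rate (131 × 0.50 + 260 × 0.65)/391 = 0.5997, s₀ = 0.0525, s₁ = 0.0528. This gives z = 1.207 and power 88.6%. With the correction, δ becomes 0.15 − 0.0057 = 0.1443, z = 1.098 and power 86.4%.

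| Evaluable | 50% vs 65%, uncorrected (corrected) | 50% vs 57.5%, uncorrected (corrected) |
|---|---|---|
| 200/200 | 92.0% (90.4%) | 44.4% (40.5%) |
| 195.5/195.5 (230/230 less 15%) | 91.5% (89.7%) | 43.7% (39.7%) |
| 131/260 (154/306 less 15%) | 88.6% (86.4%) | 40.6% (36.5%) |
| 154/306 (no loss) | 92.6% (91.1%) | 45.3% (41.4%) |

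The re-split costs about 3 points under every variant. 154/306 reaches 90% only with no attrition and a 15-point effect.

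**6. What 90% would need at 1:2 (50% vs 65%, one-sided 5%).** Corrected: 148 + 296 = 444 evaluable, or 175 + 349 = 524 enrolled after dividing by 0.85. Uncorrected: 138 + 276 = 414 evaluable, or 163 + 325 = 488 enrolled.

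**7. Detectable difference at 90% power with 131/260, one-sided 5%.** 15.4 points uncorrected, 15.9 corrected.

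**8. Conditional check.** If the conclusion is read from a two-sided 95% interval, 1.960 replaces 1.645. Power at 131/260 for 50% vs 65% is then 81.4% (78.3% corrected), and the detectable difference is 17.0 points (17.5 corrected).

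**The case against.** Several points on the other side have weight.

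- **The loss is modest.** It is about 3 points, and the uncorrected 88.6% is only 1.4 below target. The 1:2 ratio is openly justified by clinic staffing. This stands as a limit on importance, but it does not make the sentence true. The uncorrected formula asks for 185 per group, so it is not the one that gives the protocol's 200; the one that does gives 86.4%.
- **The attrition slip is small.** It is 6 women per group and about half a point of power. That stands; it is a note beside the main point.
- **The effect-size wording matters more.** Also right. On the literal text there was no 90% to maintain, because even 200/200 gives about 44% (40% corrected). Power still falls with the re-split on that reading, but no corrected figure should be printed until the effect is settled.
- **Sidedness.** A reader might infer that the planned analysis really has 78–81% power, or that the primary test must become two-sided, because section 4.3 reports 95% intervals. The protocol does not support either. The hypothesis is directional in sections 2.2 and 4.3, in line with the one-sided sizing. Section 4.3 does not say that the interval is two-sided or that it decides success, and the clause on intervals sits in a sentence about demographic drivers of the outcome. One-sided 5% sizing alongside 95% intervals is a possible mismatch of reading, not an arithmetic error.

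**Conclusion.** The statement that power is maintained at 154/306 is wrong under every reading of the effect, because the total was not raised for unequal allocation. The re-split costs about 3 points. Delivered one-sided 5% power for about 131/260 evaluable women is 89% uncorrected or 86% corrected if 15 percentage points was meant, and 41% or 37% if the 15% is relative as written. The attrition formula is also short, with minor effect.

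These figures assume the stated 50% control rate, attrition of exactly 15% in both arms, a simple two-proportion comparison, and that the printed β of 0.9 means 90% power. The 78–81% figure holds only on the further assumption that a two-sided 95% interval decides the conclusion.

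A reader might also infer that 1:2 allocation is itself a fault or that recruitment must rise. Neither follows. The ratio is a declared logistical choice, and what is wrong is the power attached to it.

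**What to change.** In section 4.1, in this order:

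1. State whether the 15% is relative (50% to 57.5%) or absolute (50% to 65%).
2. Delete the claim that power is maintained. Give 154/306 enrolled, about 131/260 evaluable, and the power for the chosen effect: about 86–89% one-sided 5% for 50% vs 65%, or about 37–41% for 50% vs 57.5%. Name the formula used.
3. Correct the attrition inflation to n/(1 − 0.15).
4. Label 0.9 as power, not β.
5. If the conclusion will be read from a two-sided 95% interval, state that power as well (about 78–81% for 50% vs 65%). Otherwise match the interval to the one-sided 5% test, as a two-sided 90% interval or a one-sided 95% bound.

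Detectable differences, if quoted, should be on one basis: for one-sided 5%, 15.4 points uncorrected or 15.9 corrected; for a two-sided 95% interval, 17.0 or 17.5.

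The cost is protocol wording and a less favourable stated power. No extra enrolment is required. If the sponsor wanted 90% one-sided power for 50% vs 65% at 1:2, the 488 to 524 enrolled would lie within the 600 projected in section 4.2, but that is optional.

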### 4.2 Feasibility

It is estimated that the number of deliveries at our catchment hospitals is approximately 3200/year at each site. Assuming that at least 55% of those women qualify for the study, there will be an average of 10 eligible patients/day during the study period. We anticipate a response rate of 50% and expect to

enroll an average of 5 women per day, 6 days a week. The anticipated total number of patients who qualify to be enrolled in the study is 5 patients x 6 days x 4 weeks x 5 months = 600 (Figure 2). Therefore, even with unexpected events or lower than expected daily recruitment capacity our final estimated sample sizes should be sufficient to recruit enough participants for the on-time completion (8 months) of the study.

Figure 2: Flow chart of expected study participant recruitment

[figure not shown]

